As tinnitus often originates from peripheral and central auditory mechanisms [13,14], the assessment of abnormal neural activity may be a potential approach for objective diagnosis. A number of research groups have suggested that tinnitus is accompanied by changes in the brain [15-20] and can be examined using electroencephalography/magnetoencephalography (EEG/MEG) [17,19,21-27]. In particular, spontaneous brain oscillations, that is, the ongoing brain activity in the absence of external events, have been intensively investigated using EEG/MEG. Traditional EEG/MEG power bands of resting-state activity have been quantified between people with tinnitus and controls [17,22]. One theory explaining group differences in the EEG/MEG power within specific frequency bands focuses on the thalamocortical dysrhythmia model. This model predicts an increase of power in low frequencies (delta and theta bands) and high frequencies (gamma band) in the auditory cortex in subjects with tinnitus [18]. Furthermore, marked alterations of EEG/MEG oscillations across other brain regions and power bands have been reported in the prefrontal cortex [28-31], cingulate cortex [29-38], parahippocampus [15,26,31,34,36,37,39-42], and insula [26,37,43], implying the involvement of other brain areas and power bands. Nevertheless, poor matching of gender, age, and hearing loss status across groups, as well as other confounding factors, hinder the interpretation of study findings and generate inconsistencies [44]. To minimize variance across subjects, a within-subject measurement comparing the brain activity during a baseline period (tinnitus with abnormal brain activity) with a period after the suppression of tinnitus (stabilization of abnormal activity) may overcome this limitation.

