This study aims to examine the brain activity in tinnitus and nontinnitus subjects using whole-scalp EEG recordings. RI will be used to modulate the tinnitus perception and enable a within-subject comparison. In addition, the RI stimuli will be matched with the tinnitus frequency of each participant, while the same low-frequency (0.5 kHz) control stimuli will be presented to all participants to exclude any effects of nonspecific sound-induced responses. We extend the applicable frequency range up to 13 kHz to enable a more accurate frequency identification of tinnitus and RI characteristics across a wider portion of the audibility range. Moreover, including nontinnitus subjects enables to compare between matched tinnitus and nontinnitus groups (ie, hearing loss characteristics) to determine whether the observed differences in the neuronal activity after RI are tinnitus-specific.

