#### Participants and Eligibility Criteria

To participate in this study, tinnitus participants have to fulfill the following inclusion criteria: (1) age ≥18 years; (2) subjective tinnitus, that is nonfluctuating; (3) a single-pitched tinnitus perception that is unilateral, bilateral (in both ears), or central (in the head); (4) a difference between the loudness discomfort level (LDL) and minimum masking level (MML) of at least 20 dB; (5) “mild” to “severe” tinnitus, that is, a Tinnitus Handicap Inventory score between 18 and 76 [51]; and (6) sensitivity to RI, that is, a reduction of at least 2 points on a Likert scale of tinnitus loudness change (−5 to +5) directly after the presentation of the acoustic stimulus and for that reduction to be repeated at least 7-10 presentations (see section “Residual Inhibition”).

The exclusion criteria for tinnitus subjects are as follows: (1) LDLs preventing RI stimulation (see section “Tinnitometry”); (2) a history of central nervous system, cardiac, neurologic, psychiatric, or other major diseases or drug abuse, deemed clinically significant at the time of the study by the investigator (Multimedia Appendix 1 for details); (3) moderate or severe depression or generalized anxiety indicated by a Hospital Anxiety and Depression Scale score of at least 11 points on either subscale [52]; and (4) any participant who experiences RI after the 0.5 kHz control stimulus.

Non-tinnitus controls need to meet the following criteria for the study inclusion: (1) age≥18 years; (2) no tinnitus defined by self-reporting; and (3) comparable audiogram to one of the tinnitus subjects, that is, within ±15 dB at each of the frequencies of the extended air conduction hearing thresholds. The values can exceed this threshold at a maximum of 2 frequencies but not at the tinnitus pitch and control frequency.

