**Figure 1 figure1:**
[figure not shown]
Overview of the electroencephalography recording procedure. RI: residual inhibition.

Subjects are blinded with respect to the order of the stimulation sequence. In the “Poststimulus” epoch, spontaneous resting-state EEG will be recorded for 40 seconds. Tinnitus subjects will be asked to indicate the return of their tinnitus to the normal loudness level by a button press and stay with minimal movement until the end of this epoch. Non-tinnitus controls will be asked to press a button immediately after they perceived a narrow-band stimulus with a central frequency and sensation level same as their matched tinnitus subjects. The stimulus has a duration of 3 seconds and will start 37 seconds after turning off the RI or control stimuli. This process will minimize bias by performing a similar task as tinnitus subjects. In the “Feedback” epoch, EEG recording will be stopped, and participants will be asked to rate the degree of tinnitus loudness change immediately after the stimulus presentation, as well as the change of psychological condition on a scale from −5 to 5 (−5 indicating quieter or feeling less burdened, 0 indicating no change, and +5 indicating louder or feeling more burdened) using the response box. The duration of this epoch is approximately 10 seconds.

Several steps will be taken to suppress or reduce artifacts during EEG recording. The acoustic chamber is electromagnetically shielded. The measurement amplifier is connected by a fiber optic data transfer to the measurement computer outside of the chamber. Before EEG recording is started, light and all power lines will be switched off and no electrical devices, except the battery-powered EEG amplifier, will be active inside the chamber In addition, the chamber will be air-conditioned to avoid contact artifacts of electrodes caused by sweating. During the assessment, participants will be asked to sit relaxed with their eyes closed; they will be instructed to move their body or eyes as little as possible to minimize motion artifacts, especially when making a button press response. To account for muscle and eye artifacts, EOG or EMG are additionally recorded.

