#### Statistical Analysis

Descriptive statistics will be used to report demographic and baseline characteristics. Quantitative data will be presented as mean, SD, and range (minimum and maximum); qualitative data will be presented as absolute and relative frequencies and, if appropriate, as graphs. We plan to use a linear mixed-effects model to test within-subject and between-group differences in traditional EEG power bands, with the participant group (ie, “tinnitus subject” and “nontinnitus subject”), time-point (ie, “baseline,” “stimulus,” and “poststimulus”), and stimulus type (ie, “RI stimulus” and “control stimulus”) as fixed effects. Subject IDs will be included as a random effect to account for repeated measures. Missing data will not be replaced but treated as “missing” values.

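### Secondary objectives 2 and 3 compare groups matched on the audiogram only, and the stated model adjusts for neither age nor sex

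*Protocol article*

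**What the plan says.** The Introduction (Background) explains inconsistent earlier findings this way: "poor matching of gender, age, and hearing loss status across groups, as well as other confounding factors, hinder the interpretation of study findings". It then describes this study's control group as allowing the investigators to "compare between matched tinnitus and nontinnitus groups (ie, hearing loss characteristics"), so hearing is the only matching factor it names.

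Participants and Eligibility Criteria agrees with that. "Non-tinnitus controls need to meet the following criteria for the study inclusion: (1) age≥18 years; (2) no tinnitus defined by self-reporting", and the third criterion is a "comparable audiogram to one of the tinnitus subjects". Comparable means within ±15 dB at each frequency, with up to two exceptions, neither of which may be at the tinnitus pitch or the control frequency. No age band or sex rule is given.

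The link between a control and a tinnitus subject is individual. In the Electroencephalography section (text after Figure 1), the control's button-press stimulus has a "central frequency and sensation level same as their matched tinnitus subjects".

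Statistical Analysis names a linear mixed-effects model with group, time-point "and stimulus type (ie, “RI stimulus” and “control stimulus”) as fixed effects", and subject ID as the random effect. Age, sex and matched set do not appear. Secondary objectives 2 and 3 (Objectives) are differences in PSD between the two groups, at baseline and poststimulus respectively.

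**The concern.** The study is observational, so group membership is not randomised, and recruitment is partly by advertisement. Of the three factors that the article says make earlier group comparisons hard to interpret, one (hearing) is handled by matching. The other two (age and sex) are handled neither in the design nor in the stated model. If controls are systematically younger or older than tinnitus subjects, or differ in sex mix, and band power varies with age or sex, the group difference in objectives 2 and 3 carries that imbalance. Depending on direction, it could mimic a tinnitus effect or hide one.

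A second, smaller matter is that the individual link between control and tinnitus subject is not carried into the model.

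**Working it through.** **1. The plan's own figure.** Sample Size gives theta-band means of 15.6 and 14.3 µV² (difference 1.3), pooled SD 0.5, two-sided 0.05, 80% power and 39 per group. The normal formula gives n = 2 × (1.96 + 0.84)² × 0.5² / 1.3² = 2.3, so 3 per group. The exact two-sample t calculation gives 3.59, so 4. The stated 39 does not reproduce. It corresponds to a standardised difference of about 0.64, that is, an SD of 1.3 / 0.6426 = 2.02. The present point does not depend on this, but it leaves the relevant SD uncertain, so both 0.5 and 2.02 are used below.

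**2. Which contrasts are exposed.**
- Baseline versus poststimulus within a subject (primary objective): age and sex are constant within the person, so they cannot confound it.
- Group-by-time contrasts (whether a change after RI is specific to tinnitus): effects of age or sex that are additive on the analysed scale cancel.
- Simple group differences at baseline or poststimulus (objectives 2 and 3): nothing cancels, so these are exposed.

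**3. Size of a possible shift.** Bias in the unadjusted group difference = (age gap / age SD) × age-power correlation × SD of power. Assumptions, none of them in the documents: gap 5 years, age SD 15 years, correlation 0.3.
- In SD units: (5 / 15) × 0.3 = 0.10.
- With SD 0.5: 0.10 × 0.5 = 0.05 µV², and 0.05 / 1.3 = 4%.
- With SD 2.02: 0.10 × 2.02 = 0.20 µV², and 0.20 / 1.3 = 16%.

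**4. Effect on the test.** At 39 per group, a bias of b SD units gives noncentrality b / √(2/39). Two-sided type I error at nominal 0.05:

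| Imbalance (SD) | Correlation | Bias (SD) | Type I error |
|---|---|---|---|
| 0.25 | 0.2 | 0.05 | 0.055 |
| 0.5 | 0.2 | 0.10 | 0.072 |
| 0.5 | 0.3 | 0.15 | 0.100 |
| 1.0 | 0.4 | 0.40 | 0.415 |

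The 5-year case in step 3 has a bias of 0.10 SD, as in the second row, and so a type I error of 0.072. The last row is an extreme: with the assumed age SD it means a 15-year gap.

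**5. Leaving out the matched set.** For one-to-one pairs with within-pair correlation ρ, the true standard error of the group difference is √(1 − ρ) times the unpaired one, so the unpaired one is overstated by 1/√(1 − ρ) − 1. This is 5.4% at ρ = 0.1, 11.8% at 0.2 and 19.5% at 0.3 (ρ assumed). In a simulation of 39 pairs (40,000 runs, standardised difference 0.64):

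| ρ | Size, unpaired | Power, unpaired | Power, paired |
|---|---|---|---|
| 0.1 | 0.038 | 82% | 83% |
| 0.3 | 0.019 | 84% | 91% |
| 0.5 | 0.007 | 88% | 98% |

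The unpaired test is conservative and loses some power. It is not biased.

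**The case against.** **The article already has a remedy.** Directly after criticising poor matching, it proposes within-subject measurement, and its primary objective uses that. This stands, and it limits the point to objectives 2 and 3. It does not protect those two objectives.

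**The audiogram stands in for age.** Matching up to 13 kHz will constrain age to some extent. But the article lists presbycusis and noise trauma as separate causes of cochlear damage, so similar audiograms can occur at different ages. Nothing in the criteria secures balance in sex.

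**The full analysis plan may add covariates.** It may, and a condensed article need not give every detail. Here, though, the article names its fixed effects and its random effect, and following that model leaves the exposure open.

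Three stronger readings are tempting, and the documents do not support them.
- *A reader might infer that the matching is thrown away.* Balance on hearing is achieved by selecting the controls and stays whether or not a matched-set term is fitted. Only efficiency is lost.
- *A reader might infer a much larger bias.* Assuming band power changes by 5% to 10% per decade, a 5-year gap moves the contrast by 2.5% to 5%, which is 28% to 55% of the planned 9.1% (1.3 / 14.3). With an age SD of 15 years, that slope gives an age-related SD of 14.3 × 0.05 × 1.5 = 1.07 to 14.3 × 0.10 × 1.5 = 2.15 µV². The stated total SD is 0.5, so the implied correlation would be 2.1 to 4.3, which is impossible. Even against 2.02 it would be 0.53 to 1.06. One caveat is that the age spread in the earlier study is not given.
- *A reader might treat chance imbalance as bias.* With an age SD of 15 years, the age gap has a standard error of 15 × √(2/39) = 3.4 years by chance alone. That is ordinary sampling variation and is already in the unadjusted standard error. Bias needs a systematic gap. The documents show no such gap, but they do nothing to prevent one in age or sex.

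**Conclusion.** The point holds for secondary objectives 2 and 3. Controls are matched on hearing only, and the stated model adjusts for neither age nor sex, which are two of the three factors the article itself blames for uninterpretable group comparisons. A systematic difference in either could be read as a tinnitus effect.

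The size cannot be known from the documents. On the assumptions in step 3 it is about 4% to 16% of the planned difference, with a type I error of about 0.07 at 39 per group. A smaller or larger imbalance moves this as the first table shows. The primary objective is untouched. Omission of the matched set is a separate and lesser matter of efficiency, and its cost depends on a within-pair correlation that is unknown and may be near zero.

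**What to change.** In Statistical Analysis, add age (continuous) and sex as fixed effects in the model used for the between-group contrasts of objectives 2 and 3, and specify this before those contrasts are examined. Age is already needed for eligibility. Sex is taken to be among the demographic characteristics the article plans to report. The cost is a sentence of wording and two degrees of freedom.

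As an efficiency measure, include a matched-set ID as a random effect above subject. A set rather than a pair also covers a tinnitus subject matched to more than one control, which the eligibility wording allows. The cost is one variance component, which may be estimated near zero. If so, the result is essentially that of the model without it.

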## Introduction

### Background

About 10%-15% of the general population is suffering from chronic subjective tinnitus, that is, consciously perceiving sound without the presence of physical sound sources [1]. Tinnitus can lead to health problems, distress, and psychological complaints and can substantially impair the quality of life [2]. In most cases, tinnitus occurs after cochlear damage such as sensorineural hearing loss [3], presbycusis [4], excessive noise exposure, and noise trauma [5]. Chronic tinnitus is also experienced by people with otherwise normal hearing [6]. Furthermore, tinnitus can be generated by head and neck injury, infections and neck illness, drugs, and other medical conditions [5] and may also be influenced by emotional and mental conditions [7]. Extensive causes and symptoms could complicate the diagnosis and treatment of tinnitus; to improve this, studies have proposed classifying tinnitus into different subtypes according to symptoms such as perceptual characteristics, laterality, loudness, or symptom severity, as well as the presence of tinnitus-associated disorders [8-10]. Alternatively, the categorization of tinnitus has been based on the response to applied treatments [11]. Nevertheless, an incomplete understanding of the underlying pathophysiology and the presence of numerous psychosocial and environmental factors that could influence intervention results may cause heterogeneity and preclude tinnitus subgrouping. As an effect, to date, there are no singularly effective clinical evaluation and treatment methods for subjective tinnitus [12]. Moreover, the current tinnitus diagnosis heavily relies on patient-reported assessments such as questionnaires. Currently, more objective assessment methods, which could provide physiology-based measures of comparison, do not exist.

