#### Recruitment

Participants will be recruited through the outpatient clinic and tinnitus consultation at our department. In addition, advertisements will be displayed in public areas and posted on the Web. No staff members from the clinic with a dependency relationship will be recruited. Potential participants who have the willingness and ability to perform all tests required for the study will sign and date an informed consent form before the start of the study procedure.

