#### Audiometry

Standard pure tone audiometry will be performed to assess bone conduction hearing thresholds (in dB hearing level) at 0.5, 0.75, 1, 2, 3, 4, and 6 kHz and air conduction hearing thresholds (in dB hearing level) at 0.125, 0.25, 0.5, 1, 2, 3, 4, 6, and 8 kHz. In addition, an extended assessment of air conduction hearing thresholds (in dB SPL) will be performed at 9, 10, 11, 12, and 13 kHz using a custom-written script and insert earphones.

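### Controls are matched on air conduction only, so type of hearing loss can confound the between-group EEG contrasts; the bone-conduction data already collected allow a cheap check

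*Protocol article*

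**What the plan says.** Under Participants and Eligibility Criteria, a control must be an adult, must have "no tinnitus defined by self-reporting", and must have an audiogram comparable to that of one tinnitus subject. Comparable is defined as "within ±15 dB at each of the frequencies of the extended air conduction hearing thresholds", followed by one relaxation: "The values can exceed this threshold at a maximum of 2 frequencies but not at the tinnitus pitch and control frequency". No type-of-loss condition is listed. The exclusion list opens with "The exclusion criteria for tinnitus subjects are as follows", and none of its items concerns conductive or middle-ear loss.

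The Audiometry section adds a second kind of threshold: "Standard pure tone audiometry will be performed to assess bone conduction hearing thresholds", at seven frequencies from 0.5 to 6 kHz. These values do not return in the eligibility criteria, the matching rule or the model. Statistical Analysis names group, time-point and stimulus type as fixed effects and subject as the random effect.

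The Introduction (Background) gives the reason for matching. Including controls is meant to allow the study to "compare between matched tinnitus and nontinnitus groups (ie, hearing loss characteristics"), and so to judge whether differences after residual inhibition are specific to tinnitus.

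**The concern.** An air-conduction threshold reflects the outer and middle ear together with the cochlea and the pathway behind it. Two people with the same air-conduction curve may have different types of loss, and the comparison with bone conduction separates them. The article itself puts weight on the type of loss: "In most cases, tinnitus occurs after cochlear damage such as sensorineural hearing loss". Its Background also names poor matching of hearing-loss status among the reasons why earlier EEG findings disagree.

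If some controls have conductive loss and a healthy cochlea while their tinnitus partners have cochlear loss, a group difference in power spectral density may reflect the cochlea and not the tinnitus. Secondary objectives 2 and 3 compare the groups at baseline and poststimulus, so they are directly exposed. The scenario is possible in this setting: "Participants will be recruited through the outpatient clinic and tinnitus consultation at our department", which is an otolaryngology department, although recruitment also uses public and web advertisements.

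**Working it through.** The plan gives no figure on this point, so there is nothing to reproduce. The check sets the rules side by side and then shows what they let through.

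**1. What is measured (Audiometry).**
- Air conduction, standard: 0.125, 0.25, 0.5, 1, 2, 3, 4, 6, 8 kHz, which is 9 frequencies.
- Air conduction, extended: 9, 10, 11, 12, 13 kHz, which is 5 frequencies. Total 9 + 5 = 14.
- Bone conduction: 0.5, 0.75, 1, 2, 3, 4, 6 kHz, which is 7 frequencies.
- Measured both ways: 0.5, 1, 2, 3, 4, 6 kHz, which is 6 frequencies. An air-bone gap can be formed at these 6. Two members of a pair can be compared on bone conduction at all 7.

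**2. What the matching rule uses.** It uses air conduction only. Audiometry applies the word *extended* to 9–13 kHz alone, whereas the matching rule also protects the 0.5 kHz control frequency, which implies the full range. The point holds on both readings: with 14 frequencies bone conduction is unused, and with only 9–13 kHz the range where bone conduction is measured would not be matched at all.

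**3. What a valid pair can look like (assumed values, at one frequency).** Control: air 40 dB, bone 5 dB. Tinnitus subject: air 40 dB, bone 40 dB.
- Air-conduction difference: 40 − 40 = 0 dB, so the pair passes.
- Bone-conduction difference: 40 − 5 = 35 dB, which is 35 / 15 = 2.3 times the protocol's tolerance.

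**4. What this could do to group means (assumed values).** Let p_c be the share of controls and p_t the share of tinnitus subjects with such a 35 dB gap, with everyone else matched on both measures. The difference in mean bone-conduction threshold, tinnitus minus control, is 35 × (p_c − p_t).

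| p_c | p_t | Difference |
|---|---|---|
| 0.10 | 0 | 3.5 dB |
| 0.20 | 0 | 7 dB |
| 0.10 | 0.10 | 0 dB |
| 0 | 0.10 | −3.5 dB |
| 0 | 0.20 | −7 dB |

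Every pair in every row satisfies the stated rule. The document gives neither share, so it does not settle the sign. Nor does it give a relation between bone-conduction threshold and power spectral density, so these decibels cannot be turned into a bias in the outcome.

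**5. Which contrasts are exposed.**
- Primary objective: baseline against poststimulus within the same subject. Each subject's own cochlear status is common to both periods, and no control is involved. Not exposed.
- Secondary objectives 2 and 3: power spectral density compared between groups in one period. Exposed.
- Tinnitus-specificity argument: rests on change after stimulation, with a 0.5 kHz control stimulus in both groups. A stable cochlear difference cancels from a change, but it could still modify the response to the stimulus. Exposed to a lesser degree.

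**The case against.** The strongest reply has five parts.

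- *The rule constrains a whole curve.* On the full reading a control must match at up to 14 frequencies, with at most two exceptions and none at the tinnitus pitch or 0.5 kHz. A purely conductive loss is unlikely to reproduce a sloping high-frequency loss. This stands: the gap is widest for flat or mixed losses, and the single-frequency example should not be read as typical.
- *Screening may deal with it.* Medical history covers external and middle ear disease, and audiometry takes place in the screening session, so both are to hand when eligibility is decided. The full protocol and Multimedia Appendix 1 are not shown and may hold a rule. This stands in part. The article attaches no rule to either item, and the appendix title lists central nervous system, cardiac, neurologic, psychiatric or other major diseases. A reader might infer that bone conduction plays no part in the study at all; the document supports only that no stated rule uses it.
- *Covariates belong in the analysis plan.* This stands as far as it goes, so the absence of a hearing covariate from the model is not a fault by itself. The point is the matching rule, which is stated in full with its tolerance and exceptions.
- *The mismatch can run either way.* A reader might infer a systematic bias towards a false tinnitus effect, because a conductive control has the healthier cochlea. The documents do not support that. Conductive loss is not excluded in tinnitus subjects either, and the Introduction also lists tinnitus with otherwise normal hearing and non-cochlear causes. No net direction is shown.
- *Air-conduction matching has its own purpose.* Sound is delivered by insert earphones at levels set relative to air-conducted noise thresholds. This stands, and it is a reason to keep the match and add to it.

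**Conclusion.** The stated matching rule, followed exactly, leaves type of hearing loss uncontrolled between the groups, although the data needed to examine it up to 6 kHz are collected. Secondary objectives 2 and 3 can be confounded by it, and the tinnitus-specificity argument can be to a lesser degree. The primary within-subject result is not affected, and nothing here should be read as a threat to it.

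The size is unknown. The 3.5 to 7 dB in the working assumes that 10–20% of controls have a 35 dB gap and that no tinnitus subject has one. It illustrates what the rule permits and is not an estimate; a reader should not quote it as the expected imbalance. Neither the net direction nor the resulting bias in power spectral density can be derived from the document. The conclusion assumes that no unseen part of the full protocol already restricts conductive loss. On that footing this is a cheap improvement.

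**What to change.** 1. Keep the air-conduction match.
2. In the between-group contrasts of objectives 2 and 3, adjust for each subject's mean bone-conduction threshold over 0.5–6 kHz. How the two ears are combined should be fixed before the contrasts are run. A covariate entered as a main effect shifts levels only; where the contrast concerns change after stimulation, let it interact with time-point.
3. Repeat these contrasts without pairs whose bone-conduction thresholds differ by more than the protocol's own ±15 dB tolerance, stating in advance whether the two-frequency allowance carries over. This repeat does not lean on the linearity that the covariate adjustment assumes.
4. If controls are still being enrolled, apply the same ±15 dB rule to bone conduction at 0.5–6 kHz. The abstract reports that data analysis is under way, so this step may come too late; steps 2 and 3 do not depend on it.
5. State as a limitation that bone conduction stops at 6 kHz while tinnitus pitch is matched up to 13 kHz, so cochlear status at a higher pitch cannot be checked.

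Cost: no new measurement, one extra covariate (with its interaction where change is analysed), some pairs lost in the sensitivity analysis and, under step 4, possibly fewer eligible controls. The document does not allow the number lost to be estimated.
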